### Setting

UCLH is an acute NHS trust in London, England and tertiary referral centre for SCT. Recruitment and outpatient assessments will take place at the University College Hospital (UCH) Macmillan Cancer Centre. Weekly visits to attend the pre-transplant intervention exercise will take place at UCLH in a gym setting. Exercise and assessments during admission for autologous transplant will take place either in the UCH Macmillan Cancer Centre or on the haematology inpatient wards at UCH.

### Recruitment procedures

A participant information sheet (PIS) detailing the study will be provided in a clinical information pack routinely posted to patients prior to their first routine transplant clinic appointment. Potential participants will be contacted by the principle researcher or study physiotherapist, with a follow-up telephone call to allow patients to ask questions about the study. Those who wish to proceed will be asked to provide informed consent and this will be recorded on the participant consent form. Those approached to take part in the study who are subsequently found to be ineligible or decline to take part will be recorded in a screening log by the principle investigator.

It is conservatively estimated that approximately 60–75 patients will be recruited over a 15–18-month period, with completion of final follow-ups within 18–21 months. Approximately 100 myeloma patients undergo ASCT at UCLH each year.

### Randomisation procedures and blinding

Participant randomisation will be undertaken centrally by a researcher not involved in outcome assessment or intervention delivery, using minimisation, with age and gender as the stratification factors using MinimPy, a free, open-source, desktop programme (https://sourceforge.net/projects/minimpy/). This researcher will communicate their allocation of participants to the physiotherapist who will inform participants of the allocation and deliver the intervention to those in the intervention arm. The principle investigator will attempt to remain blinded to group allocation and will conduct follow-up outcome assessments.

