**Methods and analysis:**

PERCEPT is a single-site, pilot randomised controlled trial of an exercise intervention embedded within the myeloma ASCT pathway, compared with usual care. The primary study end points will be feasibility measures of study and intervention delivery including recruitment rates, acceptability of intervention, study completion rate and any adverse events. Secondary end points will evaluate differences between the exercise intervention group and the usual care control group in cancer-related fatigue, quality of life, functional capacity (6 min walk test; handheld dynamometry; a timed sit-to-stand test) and objective and self-reported physical activity. Outcomes will be assessed at four time points, approximately 6–8 weeks prior to SCT, on/around day of SCT, on discharge from SCT hospital admission and 12 weeks post-discharge. The exercise intervention comprises of partly supervised physiotherapist-led aerobic and resistance exercise including behaviour change techniques to promote change in exercise behaviour. The primary outcomes from the trial will be summarised as percentages or mean values with 95% CIs. Group differences for secondary outcomes at each time point will be analysed using appropriate statistical models.

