In phase 3, when the participants have been discharged from hospital they will be advised by the physiotherapist to continue the independent exercise programme, tailored to their fitness on discharge, until they are 12 weeks post-ASCT. During these 12 weeks, they will be contacted once per week via telephone by the physiotherapist to provide support and guidance with continuing to exercise regularly during their recovery and to assist them in progressing their exercise programme. The participants will be encouraged to meet recommended guidance for levels of PA^29^ and requested to record any exercise undertaken in their log books.

Previous systematic reviews and meta-analyses have shown that BCTs from exercise interventions that are associated with improved adherence to exercise by cancer survivors include ‘goal setting (behaviour)’, setting ‘graded tasks’, and ‘instruction of how to perform behaviour’^30 31^ practice and self-monitoring and encouraging participants to attempt to generalise exercise behaviours learnt in supervised exercise environments to other, non-supervised contexts.^32^ According to the BCT Taxonomy v1, strategies to promote adherence to the intervention and promote change in exercise behaviour in the current intervention have been coded.^33^ See table 1 for incorporated BCTs and examples of how they have been included in the intervention. Physiotherapists who deliver the intervention will receive training, clinical supervision and will be provided with a standard operating procedure to carry out the intervention and support the participants to exercise and incorporate BCTs.

**Table 1 T1:** BCT coded to BCT taxonomy (BCTT V1) Michie *et al*, 2013^33^

BCT label	BCT no. (BCTT v1)	Component of intervention
Goal setting (behaviour)	1.1	Overarching goal of exercise programme for all participants is to exercise three times per week. Participants also supported to define own personal subgoals, which are recorded in log book.
Problem-solving	1.2	Enablers, barriers and solutions to barriers completed with physiotherapist and recorded in log book. Problem-solving with physiotherapist if discrepancy between current behaviour and goal is identified.
Action planning	1.4	Attendance at supervised exercise session in gym planned for specific day each week. Participants are also supported to plan independent exercise sessions (eg, time/day of the week) with physiotherapist. These plans are recorded in log book prior to planned execution.

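### The protocol lets the study physiotherapist, who is told allocations in both arms, make pre-consent contact under two-factor minimisation at a single site, so the next arm can be guessed better than chance

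*Protocol article*

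**What the plan says.** All statements are in the Protocol article.

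- **Who allocates** (Randomisation procedures and blinding): "Participant randomisation will be undertaken centrally by a researcher not involved in outcome assessment or intervention delivery".
- **How the arm is chosen** (same section): the method is minimisation on two factors, given in these words: "using minimisation, with age and gender as the stratification factors using MinimPy".
- **Who learns the result** (same section): "This researcher will communicate their allocation of participants to the physiotherapist who will inform participants of the allocation and deliver the intervention". Because the physiotherapist informs participants in general and treats only the exercise arm, this covers allocations in both arms.
- **Who makes first contact** (Recruitment procedures): "Potential participants will be contacted by the principle researcher or study physiotherapist, with a follow-up telephone call".
- **Order of events** (same section): consent comes after that contact: "Those who wish to proceed will be asked to provide informed consent".
- **Scale**: "PERCEPT is a single-site, pilot randomised controlled trial" (Abstract), and "approximately 60–75 patients will be recruited over a 15–18-month period" (Recruitment procedures).

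No section keeps a physiotherapist who has been told earlier allocations away from pre-consent contact.

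**The concern.** A central allocator keeps the allocation list out of the recruiter's hands. It does not stop the next allocation being inferred from earlier ones, and minimisation is open to that because each assignment depends on the running balance. Here there are only two factors, both known from a referral, and one site, so one person can hold the whole history. If that person also speaks to candidates before they decide, the firmness of the invitation could vary with the arm expected.

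Two results are exposed:

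- **Between-arm comparisons** of fatigue, quality of life, function and activity (Data analysis). If the kind of patient who joins differs by expected arm, the arms could differ at entry on characteristics other than age and gender. Adjusting for those two covariates would not remove this.
- **The recruitment rate.** Outcome assessment sets a target above 50% of those eligible and approached, and this is the only feasibility measure given a numerical target. Uneven encouragement could move it in either direction.

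There is also room for judgement at screening. The research team helps to decide who is clinically able to exercise regularly (Inclusion and exclusion criteria).

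**Working it through.** The plan states no figure for predictability, so there is none to reproduce. The check asks how often a caller with given knowledge would guess the next arm.

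**Inputs from the Protocol article:** minimisation on age and gender; one site; 60–75 participants.

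**Assumptions, because the article does not give them:** 1:1 allocation; 2, 3 or 4 equal age bands; gender split 60:40; imbalance measured as the sum of absolute marginal differences with equal weights; ties broken 50:50. The probability p of assigning the arm that reduces imbalance is varied from 1.0 (deterministic) to 0.5 (simple randomisation).

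**Step 1: full knowledge.** The guesser knows every earlier participant's age band, gender and arm, as well as the cut-points and the rule. With t the share of tied allocations,

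P(correct) = 0.5 × t + p × (1 − t).

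For N = 60 and two age bands, the simulated tie shares give:

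- p = 1.0, t = 0.284: 0.142 + 0.716 = 0.858
- p = 0.8, t = 0.259: 0.1295 + 0.8 × 0.741 = 0.722 (simulated 0.720)
- p = 0.7, t = 0.263: 0.1315 + 0.7 × 0.737 = 0.647 (simulated 0.644)

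**Step 2: partial knowledge.** Two weaker guessers were simulated. One knows only the running arm totals and picks the smaller arm. The other knows only the last allocation and picks the opposite arm.

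**Results, ranges over N = 60 and 75 and 2–4 age bands:**

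| Caller's knowledge | p = 1.0 | p = 0.8 | p = 0.7 |
|---|---|---|---|
| Full history, cut-points and rule | 85–86% | 71–72% | 64–65% |
| Arm totals only | 68–71% | 61–63% | 58–59% |
| Last allocation only | 62–67% | 55–57% | about 53% |
| No allocations known | 50% | 50% | 50% |

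At p = 1.0 with full knowledge, 69–72% of allocations are certain and the remaining 28–31% are ties. At p = 0.9 the full-knowledge figure is 78–79%. Sample size and number of age bands hardly matter. What matters is p and how much the caller knows.

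**Step 3: which change removes the problem.** Moving down the table brings the caller to 50% at every p. Moving across it only lowers the advantage: at p = 0.7 a fully informed caller is still right about 64% of the time. Separating the roles is therefore the effective remedy.

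**The case against.** The strongest reply has four parts.

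1. **No deterministic rule is stated.** A reader might infer from the silence on a random element that assignment is deterministic and the next arm largely predictable. The article does not support that. Assignment probability, age cut-points and weights are settings that an article commonly leaves to the full protocol, so their absence is no defect. This stands: the 85% figure is a worst case, not a description of the trial.

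2. **The overlap is not certain.** Contact is by the researcher or the physiotherapist, and the Intervention section uses the plural: "Physiotherapists who deliver the intervention will receive training, clinical supervision". The caller need not be the person who holds the allocations. This also stands, but the recruitment and randomisation sections each use the singular, and nothing divides the work. The overlap is permitted.

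3. **Guessing takes effort.** The caller must track earlier participants and, for the highest figures, know the cut-points and the rule. This is true, and it is why the range runs down to about 53%. Even so, knowing only the arm totals gives 58–71%.

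4. **This is an unpowered pilot with feasibility endpoints.** Patients receive the information sheet by post before the call, and those approached who decline or prove ineligible are logged, which protects the denominator. These points limit the damage but do not close the route. The recruitment rate is itself a primary measure, between-arm differences are to be analysed, and the Discussion presents the design as one to replicate in a powered multicentre trial.

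**Conclusion.** The weakness is real and comes from stated procedure: someone told earlier allocations in both arms may make pre-consent contact, at one site, under minimisation on two easily known factors. Such a caller would guess the next arm correctly between about 53% and 86% of the time, against 50% without that knowledge. Where the true figure lies depends on the assignment probability and on what the caller tracks, neither of which the article gives. The range also rests on the assumed age bands, gender split, 1:1 ratio and imbalance rule, though it hardly moves across the age bands and sample sizes tried.

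The effect on results is a possibility only. Neither the direction nor the size of any bias in recruitment or in the between-arm comparisons can be derived from the documents, and nothing in them shows that anyone used past allocations in this way. A reader might infer that the trial is biased; the documents support only that it could be. The point merits correction because the remedy is cheap and works at any assignment probability.

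**What to change.** In Recruitment procedures, restrict pre-consent contact and consent-taking to a team member who is not told allocations, and state that the physiotherapist meets participants only after allocation. The principal researcher is already named as a caller and could take this on, provided this is the same person as the investigator who is to attempt to remain blinded. The article does not say so, and it should be confirmed.

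Recruitment began in June 2019 (Anticipated dates of trial commencement and completion), so the change applies to remaining recruitment and to the later trial. For participants already enrolled, report who made the pre-consent contact and whether that person had been told earlier allocations.

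The cost is a change of wording with no extra staff. The drawback is that the physiotherapist can no longer cover recruitment calls, so the load falls on one role. The minimisation settings need not change for this fix to work.

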### Intervention

The intervention will involve a partly supervised exercise intervention, incorporating behaviour change techniques (BCTs), delivered by a physiotherapist and individually tailored to the ability of each participant. The intervention will involve aerobic and resistance exercise during three phases of the ASCT pathway:

Phase 1 (6–8 weeks before hospital admission for ASCT): Participants will receive one exercise session per week, supervised by a physiotherapist, at a UCLH gym. Participants will be requested to complete two further sessions per week independently.Phase 2 (during hospital admission): Participants will be offered supervised exercise sessions with a physiotherapist in the hospital setting three times per week.Phase 3 (12 weeks after hospital discharge): Participants will be asked to continue exercising independently three times per week and will receive a weekly phone call from a physiotherapist for support and guidance.

Supervised aerobic exercise will comprise of treadmill walking or stationary cycling. Participants will be encouraged to use walking as their aerobic exercise activity, or a stationary bike or elliptical trainer if they have access to one, for independent exercise sessions. In phase 1, prior to transplant admission, aerobic exercise intensity will be targeted between 60% and 80% of heart rate (HR) reserve (or Karvonen formula), in which target HR = [(max HR − resting HR) × % intensity]+resting HR, where maximum HR=220 − age.^26^ Duration will be started at 15 min and progressed by 5 min/week to achieve a minimum of 30 min by week 3–4. This will be further progressed to 40 min by week 5. Target HR will be monitored using HR belts and participants will also use a Rating of Perceived Exertion (RPE) Scale.^27^ The participants will be given a scale in their exercise log book, instructed in its use and advised to work to levels of exertion as determined under supervision. Participants will be encouraged to reach the target duration in one bout but in the presence of discomfort or wish to change exercise machine/method then participants will be required to complete the target duration in bouts of 15 min or more.

Resistance exercises will be prescribed to target all major muscle groups (depending on individual health and contraindications). Resistance training will be performed using body weight, progressed with weights or using elastic resistance bands of various strengths. These bands will be supplied to participants at the start of the study to allow convenient independent resistance training. Starting resistance and repetitions of the exercises will be informed by a 10-repetition maximum assessment carried out by the physiotherapist during the first session. Individually tailoring and gradual progression in resistance training will be prescribed as deemed appropriate at each exercise session by the physiotherapist according to published principles.^28^ Participants will be provided with exercise log books and asked to record what exercise they do in the books, as well as document how they feel after exercising and any reasons for not carrying out the exercise as prescribed.

In phase 2, when participants are admitted to hospital for their ASCT, they will be offered supervised exercise with the physiotherapist three times per week in the ambulatory care or hospital ward setting (depending on each participant’s clinical location), which they can decline if they wish to do so. It is anticipated that participants will be symptomatic from the effects of their ASCT, which may include nausea, gastrointestinal complaints and fatigue. They may also experience bleeding and infection as a result of thrombocytopenia and low white cell counts. Therefore the exercise intervention will be highly individualised and tailored according to participant’s capacity to carry out the exercises. Aerobic exercise will be carried out, as able, on a stationary bike in bouts of 10 min, up to a total duration of 30 min. HR will be monitored throughout and participants will be guided to exercise at a RPE (determined by RPE scale) they are comfortable with. Any exercise undertaken, declined or not possible due to clinical indication will be recorded by the physiotherapist in the participants’ log book.

In phase 3, when the participants have been discharged from hospital they will be advised by the physiotherapist to continue the independent exercise programme, tailored to their fitness on discharge, until they are 12 weeks post-ASCT. During these 12 weeks, they will be contacted once per week via telephone by the physiotherapist to provide support and guidance with continuing to exercise regularly during their recovery and to assist them in progressing their exercise programme. The participants will be encouraged to meet recommended guidance for levels of PA^29^ and requested to record any exercise undertaken in their log books.

Previous systematic reviews and meta-analyses have shown that BCTs from exercise interventions that are associated with improved adherence to exercise by cancer survivors include ‘goal setting (behaviour)’, setting ‘graded tasks’, and ‘instruction of how to perform behaviour’^30 31^ practice and self-monitoring and encouraging participants to attempt to generalise exercise behaviours learnt in supervised exercise environments to other, non-supervised contexts.^32^ According to the BCT Taxonomy v1, strategies to promote adherence to the intervention and promote change in exercise behaviour in the current intervention have been coded.^33^ See table 1 for incorporated BCTs and examples of how they have been included in the intervention. Physiotherapists who deliver the intervention will receive training, clinical supervision and will be provided with a standard operating procedure to carry out the intervention and support the participants to exercise and incorporate BCTs.

**Table 1 T1:** BCT coded to BCT taxonomy (BCTT V1) Michie *et al*, 2013^33^

BCT label	BCT no. (BCTT v1)	Component of intervention
Goal setting (behaviour)	1.1	Overarching goal of exercise programme for all participants is to exercise three times per week. Participants also supported to define own personal subgoals, which are recorded in log book.
Problem-solving	1.2	Enablers, barriers and solutions to barriers completed with physiotherapist and recorded in log book. Problem-solving with physiotherapist if discrepancy between current behaviour and goal is identified.
Action planning	1.4	Attendance at supervised exercise session in gym planned for specific day each week. Participants are also supported to plan independent exercise sessions (eg, time/day of the week) with physiotherapist. These plans are recorded in log book prior to planned execution.
Review behaviour goal	1.5	Participants review performance of exercise sessions recorded in log book against planned goals and consider modifying goals accordingly with physiotherapist in supervised exercise sessions.
Discrepancy between current behaviour and goal	1.6	Physiotherapist informs participant if there is a discrepancy between current behaviour and goal.
Feedback on behaviour	2.2	Feedback on performance of exercise programme delivered by physiotherapist during supervised exercise sessions (phases 1 and 2) and telephone calls (phase 3).
Self-monitoring of behaviour	2.3	Participants asked to record exercise carried out each week in log book. Heart rate monitoring used in supervised and independent exercise sessions to monitor behaviour being carried out at target intensity.
Biofeedback	2.6	Heart rate monitoring of aerobic exercise effort.
Instruction on how to perform the behaviour	4.1	Supervised exercise sessions with physiotherapist who instructs/teaches participant how to perform behaviour.
Information about health consequences	5.1	Physiotherapist and log book provide information about effects of exercise for health in context of myeloma.
Monitoring of emotional consequences	5.4	Participants encouraged to complete weekly reflections in log book.
Information about emotional consequences	5.6	Physiotherapist and log book provide information about effects of exercise on emotional well-being.
Demonstration of the behaviour	6.1	Physiotherapist demonstration and teaching of exercise programme in supervised sessions.
Behavioural practice/rehearsal	8.1	Exercises taught/demonstrated in supervised sessions are practiced within those sessions and independent sessions (phases 1 and 2).
Generalisation of target behaviour	8.6	Advice to perform exercise programme, learnt in supervised session, in independent sessions, during hospital admission and post-discharge.
Graded tasks	8.7	Progression of exercise sessions throughout exercise period.
Credible source	9.1	Education and prompting from a physiotherapist with expertise in myeloma/haematology and provided in log book.
Pros and cons	9.2	Prompts to consider advantages and disadvantages of exercising through discussion with physiotherapist and recording in log book.
Adding objects to the environment	12.5	Provision of heart rate monitors, resistance exercise bands and exercise programme sheets/log book for use in independent sessions.
Verbal persuasion about capability	15.1	Verbal support and supervision of physiotherapist to encourage exercise sessions before, during and after transplant treatment.

BCT, behaviour change techniques.

